## 1 Study background and rationale

### 1.1 Study background

Lung cancer is one of the most prevalent malignant tumors and the leading cause of cancer deaths in China. According to data published by the National Cancer Center in 2015, the five-year prevalence of lung cancer in China from 2006 to 2011 was 130.2 per 100,000 individuals. Approximately 80-85% of lung cancers are non-small cell lung cancer (NSCLC), with lung adenocarcinoma accounting for about 55% of cases. Most NSCLCs do not present with obvious symptoms in the early stages, leading to late-stage diagnosis in approximately 70% of patients, at which point the five-year survival rate is only 15%.

With the approval of an increasing number of targeted therapies and the wide use of next-generation sequencing (NGS) and other genetic testing technologies in the clinic, patients with lung cancer harboring targetable mutations such as *EGFR*, *ALK*, *ROS1*, and *MET* have got significant better treatment outcomes. However, for the NSCLC patients without identifiable driver gene mutations, chemotherapy remains the major treatment choice.

Clonal architecture is fundamental for the understanding of cancer biology and therapy. In the previous TRACELib001 (NCT03059641) study, we identified that circulating tumor DNA (ctDNA) could describe the clonal architecture of advanced NSCLC, and *EGFR* mutations do not always make up a dominant clone in advanced NSCLC. Moreover, *EGFR* clonal architecture was an independent prognostic indicator of the efficacy of *EGFR*-tyrosine kinase inhibitors. Whether this finding could be extended to other targeted therapy or even immunotherapy was unknown.

In recent years, PD-1 inhibitors such as nivolumab, pembrolizumab, and camrelizumab, as well as PD-L1 inhibitors such as atezolizumab and durvalumab, have demonstrated survival benefits compared to chemotherapy in various studies including Checkmate, Keynote, and Impower. Both the FDA and the National Medical Products Administration (NMPA) have approved multiple immune checkpoint inhibitors (ICIs) for clinical use, however, only a subset of patients experience long-term benefits from these treatments. Moreover, currently imaging assessments, tumor markers,

tumor mutation burden (TMB), PD-L1 expression, and circulating tumor DNA (ctDNA) are insufficient to predict therapeutic efficacy from PD-1/PD-L1 inhibitors.

## 1.2 Study rationale

Recently, a research team from Stanford University established the DIREct-On model, which combines blood TMB (bTMB), changes in ctDNA, and peripheral blood CD8+ T cells to predict whether patients will benefit from long-term treatment with PD-1/PD-L1 inhibitors. In the retrospective study, DIREct-On model could predict patients who would achieve durable clinical benefit (DCB, over 6 months) with high accuracy. Inspired by this study, we designed this prospective multicenter clinical trial to explore multimodal models that were more feasible in the clinical routine for predicting DCB of ICI treatments in non-EGFR/ALK NSCLC patients.

## 1.3 Exploratory study

While screening *EGFR*, *ALK* mutations, we might accidentally identify patients with actionable *ROS1* fusion, or *MET* exon 14 skipping mutation as well as *ALK* fusion, thus we also explore the clonal evolution with liquid biopsy in these patients treated with corresponding TKI.

## 2 Study objectives and study endpoints

| Study objectives                                                                                   | Study endpoints |
|----------------------------------------------------------------------------------------------------|-----------------|
| Primary study objective                                                                     | Primary study   |
| To establish a multimodal model to predict the efficacy of ICI treatments                          | endpoint
PFS |
| Secondary study objective                                                                   | Secondary study |
| To explore mutations associated with hyperprogression and severe toxic side effects in ICI Therapy | endpoint
OS  |
| Exploratory study objective                                                                 |                 |
| To investigate clonal evolution of tumor cells treated with ICI or TKI                             |                 |

## 3 Study design

### 3.1 description of study design

This study is a prospective multi-center real-world study designed to explore

multimodal models to predict the efficacy of first-line ICI treatments, as well as the clonal evolution of tumor cells treated with ICI or TKI in patients with advanced Non-Small-Cell Lung Cancer (Stage IIIB-IV, 8th edition TNM staging). ctDNA and PBMC-RNA analysis will be performed at preset time for patients treated with first-line ICI treatment. For the exploratory study subgroup – patients with *ROS1* fusion, or *MET* exon 14 skipping mutation as well as *ALK* fusion and treated with corresponding TKI, only ctDNA analysis will be performed at preset time.

### **3.2 Definition of end of study**

The end of the study is defined as over 70% of the patients had a progressive disease (PD) in their targeted lesion of the study. There would be interim data analysis and final study data analysis.

### **3.3 Duration and sample size**

The original plan was to commence in July 2020 and conclude participant enrollment by June 2023. (However, due to the COVID-19 pandemic, the enrollment is still ongoing)

The planned enrollment for this study was 250 participants from multiple centers, including *EGFR/ALK* negative NSCLC patients who received first-line ICI treatment, and NSCLC patients with *ROS1* fusion, *ALK* fusion or *MET* exon 14 skipping mutation treated with corresponding TKI. The sample size estimation was listed as the following: For the ICI subgroup, a novel clinical prediction model based on binary logistic regression was to be developed. Referring to the DIREct-On study, which enrolled 72 patients and developed an excellent model with 3 variants (peripheral CD8 T cell levels, ctDNA dynamics and ctDNA adjusted TMB) as input, we also planned 3 variants for the modeling. The prevalence of durable clinical benefit (DCB) from ICI treatments was around 30%-70%. With the criterion of 10 Events Per Variable (10 EPV), the minimal sample size required for the study was 60-100 patients.

For the targeted therapy subgroup, the sample size estimation was basically according to the prevalence of each target, as it was a descriptive study of clonal evolution. We planned to enrolled 100 patients treated with ALK-TKI, 25 patients treated with MET-TKI and 25 patients treated with ROS1-TKI.

### **3.4 Ethical application**

The study protocol was submitted to and approved by the Hospital Ethics Committee. All patients are required to sign an informed consent form before enrollment.

## **4 Study population**

### **4.1 Inclusion criteria**

1. Provision of informed consent
2. Newly diagnosed and histological or cytological confirmed stage IIIB-IV lung adenocarcinoma or squamous cell carcinoma patients according to the AJCC staging system. The stage IV lung cancer and brain metastasis can be diagnosed by imaging and enhanced CT respectively
3. No EGFR mutation in tissue and ctDNA
4. Received immune checkpoint inhibitors as the first line therapy
5. ECOG performance status 0-2 with expected more than 6 months of survival time
6. Willingness to comply with required protocols and give permission to use the data for clinical research and products development

### **4.2 Exclusion criteria**

1. Patients have other primary cancers
2. Patients have symptomatic brain metastasis, complications that are associated with brain metastasis or cognitive disorders
3. Patients failed in either plasma or tissue sample QC

## **5 Study procedure and statistical analysis plan**

### **5.1 Study treatment**

Patients were treated according to clinical routine. *EGFR/ALK* negative NSCLC patients who received first-line ICI treatment, and NSCLC patients with *ROS1* fusion, *ALK* fusion or *MET* exon 14 skipping mutation treated with corresponding TKI were eligible for enrollment in the study.

## 5.2 Study flow chart

[figure not shown]

Figure 1 Study flow

## 5.3 Test schedule

Table 1 Test schedule

| Entry                   | Screening 1    |               | Screening 2            | ICI/TKI treatment | After treatment ends/quit |                        | After PD follow-up |
|-------------------------|----------------|---------------|------------------------|-------------------|---------------------------|------------------------|--------------------|
|                         | Within 3 weeks | Within 1 week | Tumor mutation testing | After 1-2 cycles  | Treatment ends/quit       | ~30 days after ends or | Per 3 months       |
| Clinic visit            | ×              |               | ×                      | ×                 | ×                         | ×                      |                    |
| Informed consent        | ×              |               |                        |                   |                           |                        |                    |
| Demographic information | ×              |               |                        |                   |                           |                        |                    |
| Medical history         | ×              |               |                        |                   |                           |                        |                    |
| Physical examination    |                | ×             | ×                      | ×                 | ×                         |                        | ×                  |
| Laboratory examination  |                | ×             | ×                      | ×                 | ×                         | ×                      | ×                  |
| Radiological assessment | ×              |               |                        | Every 2-4 cycles  | ×                         |                        | ×                  |
| ECG/Echocardiogram      |                | ×             |                        | ×                 | ×                         |                        |                    |
| ECOG PS                 |                | ×             |                        | ×                 | ×                         | ×                      | ×                  |
| Inclusion/exclusion     |                | ×             | ×                      |                   |                           |                        |                    |
| Tumor/blood samples     |                | ×             |                        | ×                 | ×                         |                        |                    |
| Side effects            |                |               | ×                      | ×                 | ×                         |                        |                    |
| Response assessment     | ×              |               | ×                      | ×                 | ×                         | ×                      | ×                  |
| OS follow-up            |                |               | ×                      | ×                 | ×                         | ×                      | ×                  |

## **5.4 Patient efficacy assessment**

Efficacy assessments included PFS, OS. Primary efficacy indicators:

### **5.4.1 Primary endpoint**

Progress Free survival (PFS): PFS for stage IIIB-IV NSCLC who received first-line systemic therapy was defined from the start of first-line systemic therapy to disease progression or death. Disease progression was defined according to RECIST 1.1 criteria. The date on that patients receive their last imaging evaluation while alive and progress-free is used as the cutoff.

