### **5.4.2 Secondary endpoints**

Overall survival (OS): OS for first-line treatment, from the start of first-line treatment until death, and for surviving patients, until the date of last follow-up.

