### **5.5.2 Grouping method**

For the ICI subgroup, patients will be divided into 2 groups with 6 months PFS as the cutoff, with PFS of durable clinical benefit (DCB) group  $\geq 6$  months and non-durable benefit (NDB)  $< 6$  months, referring to the DIREct-On study.

For the targeted therapy subgroup, further grouping includes: primary resistance group (progressed in 3 months), long term benefits (PFS  $\geq 36$  months), and the rest which

could be further divided into PFS  $\geq$  medium reported PFS or not.

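### PFS and OS for the TKI subgroup start at first-line therapy, but no line is fixed for the TKI, so its resistance and benefit groups can measure an earlier drug

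*Protocol*

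**What the plan says.** **Time origin.** Protocol 5.4.1 introduces the endpoint as "PFS for stage IIIB-IV NSCLC who received first-line systemic therapy" and states that it "was defined from the start of first-line systemic therapy to disease progression or death". Section 5.4.2 runs OS "from the start of first-line treatment until death". Neither section names a drug, and neither gives the TKI subgroup an origin of its own.

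**Who enters.** For the ICI subgroup the line of therapy is fixed. Inclusion criterion 4 in section 4.1 reads "Received immune checkpoint inhibitors as the first line therapy", and section 3.1 describes the aim as "multimodal models to predict the efficacy of first-line ICI treatments". For the other subgroup, section 5.1 says that "NSCLC patients with *ROS1* fusion, *ALK* fusion or *MET* exon 14 skipping mutation treated with corresponding TKI were eligible for enrollment". Sections 1.3, 3.1, 3.3 and 5.5.1 also describe these patients without a line of therapy.

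**How the time is used.** Section 5.5.2 splits the ICI subgroup at 6 months of PFS. It divides the targeted-therapy subgroup into "primary resistance group (progressed in 3 months), long term benefits (PFS" of at least 36 months) and a remainder, which may be split further at the reported median PFS.

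**The concern.** The TKI groups are meant to describe how a tumour behaved under the TKI, so that ctDNA findings on clonal evolution can be set against them. That works only if the clock starts with the TKI. The protocol's clock starts with whatever systemic therapy came first, and its eligibility wording lets the TKI come later. A patient could then be called primarily resistant to a TKI not yet given, or be credited with benefit gained on another drug. The ctDNA results would be read against an outcome belonging to a different treatment.

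**Working it through.** **1. Is the planned size involved?**

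Inputs (sections 3.3 and 5.5.1): 10 events per variable, 3 variables, DCB prevalence 30% to 70%; TKI cohorts of 100, 25 and 25; total 250.

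- ICI model: 10 × 3 = 30 patients are needed in the rarer outcome class. 30 / 0.5 = 60 and 30 / 0.3 = 100, which reproduces the stated 60-100.
- TKI subgroup: 100 + 25 + 25 = 150. 250 − 150 = 100, the upper end for the ICI subgroup. 150 / 250 = 60%.

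None of these figures depends on the time origin, so none changes.

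**2. ICI subgroup.** The ICI has to be the first-line therapy, so the start of first-line therapy and the start of the ICI line coincide. The lag is 0 and no DCB label moves.

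**3. TKI subgroup.** Let L be the months from the start of first-line therapy to the first TKI dose, and T the months from that dose to progression or death.

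- *TKI is the first-line therapy:* L = 0, written PFS = T. The groups are correct.
- *Progression on an earlier drug, then TKI:* written PFS ends at that first progression, and T plays no part. Hypothetical case: progression on the earlier drug at month 2. Written PFS = 2 months, which is within 3, so the patient is labelled primarily resistant before any TKI exposure.
- *Switch to the TKI without progression:* written PFS = L + T.
  - The 36-month group is reached when T ≥ 36 − L. With L = 2, 34 months on the TKI is enough.
  - The 3-month group requires L + T ≤ 3. With L = 2 and T = 2, written PFS is 4 months, and a patient who progressed 2 months into the TKI escapes the primary-resistance label. With L above 3, that label cannot be reached at all.
  - The comparison with the reported median is shifted by L in the same way.
- *OS:* the written time includes L, during which the patient must have been alive in order to receive the TKI.

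The misclassification therefore runs in both directions: false resistance after early progression on another drug, and false benefit after a switch without progression.

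**4. How many patients?** The protocol gives no share of TKI patients treated after another systemic therapy, and no distribution of L. The number affected lies between 0 and 150 and cannot be narrowed from the document.

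**The case against.** The strongest reply is that the protocol, read as a whole, describes a first-line study. Section 1.3 says that these patients are found during EGFR and ALK screening. Section 4.1 asks for newly diagnosed stage IIIB-IV disease. Section 5.4.1 speaks of patients given first-line systemic therapy. Table 1 passes from screening and mutation testing straight to ICI or TKI treatment, with no column for an earlier regimen. On this reading L = 0 for everyone. It can be added that the 3-month rule stands under the targeted-therapy heading, so a sensible analyst would count from the TKI.

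This makes first-line TKI plausible and probably common, but it does not make it a requirement. The section 4.1 list also demands first-line ICI, so it cannot apply as a whole to TKI patients, and its newly-diagnosed criterion does not clearly bind them. Section 5.1 admits them under routine care on receipt of the TKI alone. An analyst who counts from the TKI departs from the only PFS definition given.

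A reader might also infer that the 6-month DCB label is contaminated, because an ICI could be added one or two cycles into the first-line regimen. As an illustration, a lag of 0.7 to 1.4 months under exponential PFS would raise the DCB share by 3.0 to 9.7 percentage points over the 30%-70% range. The protocol does not support that premise: ICI is required as first-line therapy, and no staggered start is described. Those figures are no part of this point.

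**Conclusion.** The point holds for the TKI subgroup only. The PFS and OS origin in 5.4 and the time-based groups in 5.5.2 do not fit an eligibility rule that leaves the line of the TKI open. Followed literally, the definition can mislabel any TKI patient who first received another systemic drug. If every TKI patient turns out to be treated first line, nothing is lost. This goes beyond detail left to an analysis plan, because the protocol itself fixes both the origin and the groups.

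The consequence is limited. It concerns the exploratory objective, in a subgroup that the protocol treats descriptively. It covers up to 150 of the 250 planned patients, with an unknown share affected. The primary objective, the ICI model, the DCB label and the sample sizes stand as they are.

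**What to change.** In 5.4.1 and 5.4.2, add that for the TKI subgroup PFS and OS start at the first dose of the corresponding TKI, and that only progression or death after that dose counts. In 5.5.2, state that the 3-month, 36-month and reported-median groups use this time. Leave the ICI origin and the 6-month split unchanged.

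The cost is two or three sentences of protocol wording and a TKI first-dose date from the medical record. No visits, samples or patients are added. Where the TKI is the first-line therapy, every result stays the same.

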## **5.5 Statistical analysis plan**

### **5.5.1 Sample size calculation**

For the ICI subgroup, a novel clinical prediction model based on binary logistic regression was to be developed. Referring to the DIREct-On study, which enrolled 72 patients and developed an excellent model with 3 variants (peripheral CD8 T cell levels, ctDNA dynamics and ctDNA adjusted TMB) as input, we also planned 3 variants for the modeling. The prevalence of durable clinical benefit (DCB) from ICI treatments was around 30%-70%. With the criterion of 10 Events Per Variable (10 EPV), the minimal sample size required for the study was 60-100 patients.

For the targeted therapy subgroup, the sample size estimation was basically according to the prevalence of each target, as it was a descriptive study of clonal evolution. We planned to enrolled 100 patients treated with ALK-TKI, 25 patients treated with MET-TKI and 25 patients treated with ROS1-TKI.

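### ctDNA dynamics is known only after 1-2 cycles, yet the PFS and DCB analyses that use it are not limited to patients event-free at that sample

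*Protocol*

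**What the plan says.** Protocol section 5.4.1 starts the outcome clock at treatment: PFS "was defined from the start of first-line systemic therapy to disease progression or death". It ties progression to imaging: "Disease progression was defined according to RECIST 1.1 criteria". Section 5.5.2 builds the binary outcome on the same clock: "patients will be divided into 2 groups with 6 months PFS as the cutoff".

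On predictors, section 5.5.1 describes the DIREct-On model as having "3 variants (peripheral CD8 T cell levels, ctDNA dynamics and ctDNA adjusted TMB) as input", and adds "we also planned 3 variants for the modeling". Section 5.5.3.2 says that the DIREct-On model will be recapitulated and that new multimodal models will be built by binary logistic regression. It also specifies Kaplan-Meier curves and a Cox model for each covariate.

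Table 1 in section 5.3 marks tumor/blood samples at screening, at the on-treatment visit "After 1-2 cycles", and at the end of or withdrawal from treatment. On-treatment radiology is "Every 2-4 cycles". Response assessment is marked in the same on-treatment column as the blood sample.

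**The concern.** A change in ctDNA does not exist until the on-treatment sample is drawn, but the outcome starts counting at first treatment. A patient who progresses or dies by the sample date is already NDB when the marker becomes available. The stated analyses do not exclude such patients from a model that contains the marker.

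The harm depends on how these patients are handled, and the protocol does not say.

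- **Kept**, with a ctDNA value taken at or after the event: part of the model's accuracy is concurrent detection of progression, not prediction. The draw at treatment end makes such a value available, although nothing says it would be used.
- **Dropped** for lack of a usable sample: the scored patients all have guaranteed event-free time up to the sample. Their DCB rate and PFS are then too favorable for a patient starting treatment. Every patient lost is NDB, so the events-per-variable (EPV) count changes.

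The primary objective is a model that predicts ICI efficacy, so discrimination and DCB rate are its main results.

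**Working it through.** **1. The plan's own figure.** With 3 variables and 10 EPV, 30 patients are needed in the smaller outcome class: N = 30 / min(DCB, 1 − DCB). DCB 50% gives 30/0.5 = 60. DCB 30% or 70% gives 30/0.3 = 100. The stated 60-100 is reproduced.

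**2. Events by the sample.** The protocol gives neither cycle length nor PFS shape. Assume 3-week cycles and exponential PFS calibrated to the stated DCB range of 30-70%: λ = −ln(DCB)/6 per month. A sample after 2 cycles falls at t = 42/30.4375 = 1.38 months. The share with an event by then is e = 1 − exp(−λt).

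- At DCB 50%, λ = 0.1155 and e = 1 − exp(−0.159) = 0.147.
- The NDB share left is 0.50 − 0.147 = 0.353, so N = 30/0.353, about 86.
- The DCB rate among the remaining patients is 0.50/0.853 = 0.586.

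| DCB | Event by 6 weeks | As share of NDB | NDB left per 100 enrolled | DCB rate in those left | N for 10 EPV (stated basis) |
|---|---|---|---|---|---|
| 30% | 24.2% | 34.6% | 45.8 | 39.6% | 100 (100) |
| 50% | 14.7% | 29.5% | 35.3 | 58.6% | 86 (60) |
| 70% | 7.9% | 26.3% | 22.1 | 76.0% | 136 (100) |

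With a sample after 1 cycle (3 weeks), the excluded shares are 12.9%, 7.7% and 4.0%, and N is 100, 71 and 116. Over cycle lengths of 2-6 weeks and samples at 1 or 2 cycles, the excluded share runs from 2.7% to 42.5%.

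**3. Against planned enrollment.** Section 3.3 plans 250 patients, of whom 100 + 25 + 25 receive a TKI, which leaves 100 for ICI. With 100 enrolled and the 6-week sample, EPV is 30/3 = 10.0 at DCB 30%, 35.3/3 = 11.8 at DCB 50% and 22.1/3 = 7.4 at DCB 70%.

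**4. If early events are kept.** A simulation used 400,000 patients per setting, a 6-week sample, and proportional hazards in a standardized ctDNA change. It compared the AUC for NDB in patients event-free at the sample with the AUC in all patients. Early-event values were raised by an assumed 0, 0.5, 1 or 2 SD to represent sampling at or after progression. At DCB 50%:

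| HR per SD | AUC, event-free at sample | AUC, all kept (0 / 0.5 / 1 / 2 SD) |
|---|---|---|
| 1.00 | 0.50 | 0.50 / 0.54 / 0.58 / 0.62 |
| 1.65 | 0.67 | 0.68 / 0.72 / 0.74 / 0.77 |
| 2.72 | 0.78 | 0.81 / 0.83 / 0.85 / 0.86 |

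Across DCB 30-70% the excess runs from about 0 to 0.15.

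**5. If early events are dropped.** The AUC is the event-free value, with no excess. With a common sample time, the Cox log hazard ratio was the same on either clock (0.4894 in both fits). The sample time here may vary between 1 and 2 cycles, so that exact equality need not carry over. Absolute PFS and the DCB rate are still shifted upward, as the table in step 2 shows.

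**The case against.** The case against is substantial, and much of it stands.

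- **Inflated accuracy is not established.** A reader might infer that the plan overstates discrimination as written. That follows only if patients with an event by the sample are kept and scored. No section says so, and step 5 shows no AUC excess if they are dropped.
- **Few events can precede the sample.** RECIST progression needs a scan, and scheduled scans begin at 2-4 cycles. Section 4.1 requires expected survival above 6 months. Events before a 1-cycle sample would therefore be mainly deaths or unscheduled scans. Coincidence with a scheduled scan needs the latest sample time and the earliest scan time, both at cycle 2. The shares in step 2 are thus on the high side and fit events before or at the sample better than events strictly before it.
- **The new model's inputs are not named.** Section 5.5.1 fixes their number and follows the reference model's pattern. Only the recapitulation clearly needs ctDNA dynamics; for the new model it is a likely input.
- **No baseline claim is made.** A reader might infer that the model is offered as a tool for use before treatment starts. Sections 1.2 and 2 do not say this, and section 1.2 openly describes changes in ctDNA.
- **Landmarks often belong in a separate SAP.** That is fair for the detail. But section 5.5 of this protocol itself fixes the clock, the 6-month split and the models, and these do not fit the sampling schedule for an on-treatment marker.
- **Restarting the 6-month clock would change the definition of DCB.** This is correct. It would weaken comparability with the reference model, so it is not proposed.

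**Conclusion.** The point holds in conditional form. The timing mismatch is fixed by the protocol: the outcome starts at treatment, ctDNA dynamics is known after 1-2 cycles, and the stated analyses are not limited to patients event-free at that sample. Which harm follows depends on handling that the protocol does not state: credit for progression already present, or estimates conditional on reaching the sample with a smaller NDB class.

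If early events are dropped, a DCB rate of 50% would appear as about 59% in scored patients under the 6-week assumptions. If they are kept, the AUC excess could be anything from about 0 to 0.15, depending on an assumed shift for which the documents give no value. All these figures rest on assumed 3-week cycles and exponential PFS and should be read as upper-side. The stated 60-100 is not an arithmetic error, and models using only baseline predictors are unaffected. The point merits a change in the plan; it does not undermine the design.

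**What to change.** For any Kaplan-Meier, Cox or logistic analysis that contains an on-treatment marker:

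1. Include only patients alive and progression-free at the on-treatment sample. Count progression found on a scan at the same visit as a prior event.
2. Start Kaplan-Meier and Cox time at that landmark, or use delayed entry.
3. Keep DCB as 6 months from treatment start, and state that results are conditional on being event-free at the sample.
4. Report how many patients were excluded for earlier events.
5. Adjust for, or examine in a sensitivity analysis, the time from first dose to sample.
6. Recheck 10 EPV on the remaining DCB and NDB counts.

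Baseline-only models keep the treatment-start clock.

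The change needs no new visits or samples. Section 3.3 describes enrollment as ongoing, so it can be written in before data lock. The cost is in precision: early progressors leave the on-treatment model and effective EPV falls, to about 7.4 in the least favorable case of step 3. The achieved EPV should be restated; enrolling more patients is not called for on this ground.

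### For ICI patients whose last progression-free scan falls well before month 6, the DCB/NDB label turns on whether they later die, not on evidence of their status at 6 months

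*Protocol*

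**What the plan says.** Section 5.4.1 measures PFS as "defined from the start of first-line systemic therapy to disease progression or death", with progression judged by RECIST 1.1. For patients without an event it adds: "The date on that patients receive their last imaging evaluation while alive and progress-free is used as the cutoff". So a death ends PFS on the date of death, however old the last scan is, while a living patient's time ends at the last scan.

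Section 5.5.2 turns that time into a label: "patients will be divided into 2 groups with 6 months PFS as the cutoff". DCB is 6 months or more and NDB is less than 6 months. It has no third group, and it does not require an assessment at 6 months.

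The label feeds the primary objective. Section 5.5.1 states that "a novel clinical prediction model based on binary logistic regression was to be developed", and section 5.5.3.2 repeats the logistic approach.

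In Table 1 (section 5.3), radiological assessment is marked at screening, on treatment ("Every 2-4 cycles"), at treatment end or quit, and in the column "After PD follow-up". The column about 30 days after the end of treatment has no radiology mark, although response assessment is marked there. No column covers repeat imaging for a patient who stops without progression. OS follow-up is marked in every column from the second screening visit onward.

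**The concern.** Each rule is ordinary for a time-to-event analysis. The difficulty comes from turning PFS time into a yes/no label without asking whether the patient was observed near month 6. A patient who stops early without progression may progress unseen. If that patient dies after month 6, the label is DCB. If an otherwise identical patient is alive, the clock goes back to the early scan and the label is NDB. Two patients with the same imaging, and equally unknown status at 6 months, get opposite outcomes because of vital status.

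The schedule allows this, because deaths go on being captured through OS follow-up while imaging for progression is not scheduled in this group. The errors would gather among early stoppers and so need not be random with respect to the predictors. The planned sample leaves little slack: with three predictors and 10 events per variable, the smaller class has about 30 patients.

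**Working it through.** **The plan's own figure.** Section 5.5.1 gives "we also planned 3 variants for the modeling", 10 events per variable and a DCB prevalence of 30%-70%. Taking the smaller class as events, N = 3 × 10 / min(p, 1 − p). At p = 0.5 this is 30/0.5 = 60; at p = 0.3 or 0.7 it is 30/0.3 = 100. The stated 60-100 is reproduced and is not disputed here.

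**The two rules applied to three records**, each with a clean scan at month 2:

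| Record | After month 2 | PFS under 5.4.1 | Label under 5.5.2 |
|---|---|---|---|
| A | no scan, dies at month 8 | 8 months (death) | 8 ≥ 6: DCB |
| B | no scan, alive at month 8 | 2 months (last scan) | 2 < 6: NDB |
| C | progression on a month-4 scan, dies at month 8 | 4 months (progression) | 4 < 6: NDB |

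A and B have the same imaging and opposite labels. A and C may have the same disease course and also differ. The A/B reversal occurs for any last progression-free scan before month 6 paired with a death at or after month 6.

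**Can the gap arise?** The protocol gives no cycle length. At an assumed 3 weeks, 2-4 cycles is 6-12 weeks, about 1.4-2.8 months (0.9-3.7 months across 2- to 4-week cycles). On treatment, a 6-month gap therefore means missed scans. After an early stop without progression, no further scan is scheduled.

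**Size, on assumptions.** Only the 30%-70% range comes from the protocol. Assumed: exponential progression with S(6) = 0.3, 0.5 or 0.7; a share q = 10% or 20% assigned an early stop, uniform over months 1-5 and counted only if still progression-free; no scan after stopping; median survival after progression of 6 or 10 months; deaths counted from month 6 to month 36.

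With λ = −ln S(6)/6, patients who stop without progression number q(e^−λ − e^−5λ)/(4λ), and those of them still progression-free at month 6 number q·S(6). The difference is the ceiling on mislabelled patients. A simulation of 1,000,000 patients per scenario gives those who also die between months 6 and 36. Per 100 ICI patients, for q = 10% / 20%:

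| S(6) | Stop without PD | Truly progression-free at month 6 | Ceiling | True NDB labelled DCB |
|---|---|---|---|---|
| 0.3 | 5.6 / 11.3 | 3.0 / 6.0 | 2.6 / 5.3 | 2.0 / 4.1 |
| 0.5 | 7.1 / 14.2 | 5.0 / 10.0 | 2.1 / 4.2 | 1.7 / 3.3 |
| 0.7 | 8.4 / 16.8 | 7.0 / 14.0 | 1.4 / 2.8 | 1.1 / 2.2 |

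The two survival assumptions give nearly the same counts. The range is 1.1-4.1 per 100, or about 1.5%-12% of true DCB plus mislabelled patients (for example 4.1/(30 + 4.1) = 12%). If unscheduled scans catch half of these progressions, the counts halve.

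The range is an upper one. The mislabelled patients go a median of 9-12 months from stopping to death without a scan, and 48%-62% of them die at or after month 12. Only about 0.2-1.2 per 100 die by month 9, as in record A.

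**The case against.** **Death as a PFS event is conventional.** This stands. In the Kaplan-Meier and Cox analyses record B is simply censored, and nothing needs changing there. The fault lies only in the conversion to a binary label.

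**Scan-gap rules usually sit in an SAP.** This stands in part. A detailed missed-assessment rule could be in a document not shown. But the time rule and the two-group cut are fixed in the protocol, and together they already produce the labels above.

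**The protocol never says that a living patient cut before month 6 is NDB.** True as to wording. It follows because section 5.5.2 allows only two groups, split on PFS time, and 2 months is below the cut.

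**Table 1 is weak evidence that scans stop.** This also stands in part. Response assessment is marked about 30 days after treatment ends, and section 5.1 says that care follows clinical routine, so scans outside the table are likely. They reduce the number of such records but do not remove the labelling rule. A patient who quit at month 2 and was assessed a month later would still have a last assessment near month 3.

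**Stronger readings.** A reader might infer that up to 12% of the DCB class is wrong, or that the model will end up selecting for toxicity or frailty. The documents support neither. The percentage depends on assumed stop rates and long unscanned survival with progressive disease, and no bias in coefficients or discrimination has been calculated.

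**Conclusion.** The point holds in a limited form. As written, sections 5.4.1 and 5.5.2 assign opposite labels to patients with identical imaging and unknown 6-month status, according to whether they died. That follows from the text and needs no assumption about rates.

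How many patients are affected cannot be derived from the protocol. On the stated assumptions, at most about 1-4 per 100 ICI patients are true NDB labelled DCB through late death, and probably fewer with routine scans. Living patients cut before month 6 are probably the larger group. In the same model, early stoppers who are truly progression-free at month 6 number 3-14 per 100, and those alive and unscanned fall into NDB. The late-death problem therefore belongs with the labelling of patients censored before month 6, as a lower-priority extension of it. It does not make the PFS definition or the 60-100 minimum wrong.

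**What to change.** Change section 5.5.2 only, and leave the PFS definition for Kaplan-Meier and Cox as it is:

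- **NDB:** RECIST progression or death before 6 months.
- **DCB:** a progression-free assessment at or after 6 months; or first documented progression, or death, at or after 6 months where the preceding progression-free scan is no more than one maximum scheduled imaging interval earlier. In Table 1 that interval is 4 cycles; state it in weeks, because the protocol gives no cycle length.
- **Status unknown at 6 months:** every other patient, alive or dead, with no progression documented before 6 months. Report the number, handle all of them by one common rule, and add a sensitivity analysis that keeps the present section 5.5.2 labels.

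The second route to DCB is needed. If only a clean scan at or after month 6 or a late death could qualify, a patient clean at month 5 with progression first seen at month 7 would fit neither group. In the model above, with 3-week cycles, roughly λ × interval × S(6) of patients are in that position: from 0.059 × 1.38 × 0.7 = 6 per 100 to 0.201 × 2.76 × 0.3 = 17 per 100.

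The cost is a short rule and one derived flag, using scan and death dates already collected. The downside is a smaller labelled sample, because some patients with true benefit become unclassified (the 3-14 per 100 above, if none is scanned again). If 5%, 10% or 20% of patients were excluded as unknown, keeping 30 in the smaller class would raise the 60-100 minimum to 64-106, 67-112 or 75-125 (the minimum divided by 0.95, 0.90 or 0.80, rounded up). These shares are illustrative; the protocol gives none.
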